**Methods and analysis:**

The QM2-RC encompasses three interconnected projects (Project 1, 2, and 3) aimed at developing a quality management strategy and evaluating its impact on system performance across New York State. This report specifically focuses on Project 3, which involves a stepped-wedge trial with 35 clinics receiving a quality management intervention that includes performance coaching. This intervention will be compared to a treatment-as-usual (TAU) condition for clinics not participating in the trial. Administrative data will be utilized to monitor outcomes over four years. The coaching intervention, guided by the Integrated Promoting Action on Research Implementation in Health Services (i-PARIHS) model, emphasizes interpreting quality measures and applying insights to enhance care. Coaches will provide support on data utilization, patient-centered care, harm reduction strategies, and the use of patient monitoring tools. The trial aims to evaluate clinic staff and leadership attitudes, experiences, and behaviors through surveys, semi-structured interviews, and external facilitator notes. Primary clinic outcomes will be assessed through adverse events, decreased clinic rates of substance use related emergency department visits and hospitalizations as well as mortality among patients within the first 12 months after admission to treatment after adjusting for individual and community level characteristics. This study is being developed over a multi-year period and will be informed by a mixed-methods approach incorporating multiple data sources, qualitative interviews, patient and clinic surveys. The study is being conducted in partnership with New York State Office of Addiction Services and Supports (OASAS) and will be informed by input from patient, providers, health insurers, family members and local governing units.

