Before the trial begins, clinics receiving the QM2 intervention will be randomized into six cohorts of six-month long interventions over three years. Clinics are randomized to onset of intervention in one of six time periods over the three years of the intervention rollout (years 2–4 of the project) and tracked using administrative data. Administrative data will be used for all clinic clients during each of the seven six-month periods (n ≈ 350/clinic) will be drawn from administrative data. The first six-month period will be a baseline prior to any intervention. Six clinics will be assigned randomly to one of six time periods for onset of intervention. Using administrative data, we will track clients within each clinic over four years, including a pre-intervention six-month baseline period. During the same four-year period, clients in clinics not participating in the stepped-wedge trial will be tracked to better understand changes in outcomes under treatment as usual (TAU) and to compare the outcomes of those clinics with clinics receiving the quality management intervention. We anticipate a final study population of approximately 91,000 individuals per year who are receiving treatment from one of the 571 enrolled outpatient substance use treatment programs. Because this is a stepped-wedge trial, all clinics (and as a result all clients within the clinics) will eventually get the intervention, the randomization will have to do with when the clinic is randomized rather than being assigned to a control or intervention group. Fig 2 illustrates the structure of the stepped-wedge trial.

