### Data and analytic plans

#### Project 3: Stepped-wedge trial.

*Quantitative Methods:* We will utilize Generalized Linear Mixed Models (GLMMs), which are commonly applied in the analysis of stepped-wedge trial [106,107]. The models will be structured as follows:

$$F(\mu_{ijk})=\mu +\beta_{j}+{\delta X}_{ij}+\alpha_{i}+\phi_{ik},\;\alpha_{i}\sim N\left(\text{0},\tau_{\alpha }^{\text{2}}\right),\;\gamma_{ij}\sim N(\text{0},\tau_{\phi }^{\text{2}})$$

where $\beta_{j}$ represents a fixed effect for time, $X_{ij}$ is an indicator for intervention in clinic *i* at time *j* (coded 0 for the control condition, then 1 from the start of the intervention in the clinic until the end of the study), and δ denotes the intervention effect. The models include random effects to account for clustering at both the clinic and individual patient levels, which are assumed to follow a normal distribution with mean zero and variances $\tau_{\alpha }^{\text{2}}$ and $\tau_{\phi }^{\text{2}}$, respectively. We will estimate the intervention effect while controlling for secular trends and adjusting for clustering within clinics ($\alpha_{i}$) and individual ($\phi_{ik}$), using mixed effects modeling with a binary distribution and logit link function. The models will be fitted using the *glmmTMB* package in R software [108,109]. The primary outcome will be adverse events, and the fixed-effects coefficients for the intervention effect, exponentiated, will indicate the extent to which the intervention changes the rate of adverse events. An offset term can be included to capture client differences in time at risk due to timing of treatment entry.

TAU clinics will be included in the model with an indicator variable. A post-hoc test of the intervention effect coefficient will compare TAU and performance coaching, and a TAU-by-time interaction will assess time trends within the TAU group. The GLMM analysis will be expanded by adding the clinics not receiving the performance coaching intervention during the study period. For TAU clinics, the intervention indicator will be coded 0 in all periods. This provides an additional estimate of trends ($\beta_{j}$) in outcomes in a much larger sample of clinics. Because the fixed effect for time ($\beta_{j}$) is estimated, the intervention effect (δ) can be interpreted as the degree to which performance coaching results in a lower rate of adverse events than what would be expected due to time alone in the absence of intervention.

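### The test named as the TAU-versus-coaching comparison is a test of δ, from which the TAU clinics' level cancels, so it does not compare coached with TAU clinics' outcomes

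*Protocol article*

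**What the plan says.** The Abstract (Methods and analysis) announces a comparison with outside clinics: "This intervention will be compared to a treatment-as-usual (TAU) condition for clinics not participating in the trial". Materials and methods, in the paragraph on randomisation, gives as one purpose of tracking the non-participating clinics "to compare the outcomes of those clinics with clinics receiving the quality management intervention".

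The model is set out under Data and analytic plans, Project 3: Stepped-wedge trial. In trial clinics the intervention indicator X is "coded 0 for the control condition, then 1 from the start of the intervention in the clinic until the end of the study", and its coefficient δ is defined as the intervention effect. For the other clinics the section states:

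- "TAU clinics will be included in the model with an indicator variable";
- "For TAU clinics, the intervention indicator will be coded 0 in all periods";
- "A post-hoc test of the intervention effect coefficient will compare TAU and performance coaching", and, in the same sentence, "a TAU-by-time interaction will assess time trends within the TAU group".

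The paragraph closes by reading δ as the reduction in adverse events relative to something else: "than what would be expected due to time alone in the absence of intervention". No contrast involving the coefficient of the TAU indicator is named anywhere.

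**The concern.** The article assigns a specific coefficient to a specific comparison, and the two do not match. A separate indicator for TAU clinics absorbs whatever level those clinics have. The coefficient of X is then identified from trial clinics before and after they start coaching, and at most borrows the time trend from TAU clinics.

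At stake is the interpretation of a secondary result. A significant δ, labelled as a TAU comparison, invites the statement that coached clinics do better than TAU clinics when the test says nothing about their relative outcomes. It would also look too precise, because δ does not carry the between-clinic variation that a comparison of different clinics must carry. The error can run the other way too: coached clinics may have better outcomes than TAU clinics, for instance through who volunteered, while δ is zero.

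**Working it through.** **Inputs from the article (power paragraph unless noted).** 35 clinics; 5 crossover points with 7 clinics each; 350 clients per clinic per half-year; ICC 0.05; α = 0.05 (taken as two-sided); rate 0.23; RR 0.93, so 0.23 × 0.93 = 0.2139, a difference of 0.0161. TAU clinics: 571 − 35 = 536, or 550 − 35 = 515, since the article gives both totals.

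**Assumptions.** Clients per TAU clinic per half-year are not given; I varied them from 80 to 350. TAU event rates are not given; those below are illustrations. Calculations use a linear model on the probability scale with an exchangeable clinic effect. The cancellation in step 2 is algebra on the linear predictor and carries over to the logit.

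**Step 1. Reproduce the stated figure.** 73,500 = 35 × 350 × 6, so the power paragraph implies six periods. Total variance is 0.23 × 0.77 = 0.1771, clinic variance τ² = 0.05 × 0.1771 = 0.008855, and cell-mean residual variance σ² = 0.95 × 0.1771 / 350 = 0.000481. The standard cross-sectional stepped-wedge formula is

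Var(δ) = Iσ²(σ² + Tτ²) / [(IU − W)σ² + (U² + ITU − TW − IV)τ²],

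with I = 35, T = 6, U = 105, W = 2695, V = 385. The numerator is 35 × 0.000481 × 0.05361 = 0.000902. The denominator is 980 × 0.000481 + 3430 × 0.008855 = 30.84. Hence SE(δ) = √(0.000902 / 30.84) = 0.0054. The difference detectable with 80% power is 2.80 × 0.0054 = 0.0151, an RR of about 0.93, as stated. Power at exactly RR 0.93 is Φ(0.0161/0.0054 − 1.96), about 85%.

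**Step 2. What δ contrasts.** Write θ for the TAU indicator and λ_j for the TAU-by-time term in period j. The linear predictors in period j are:

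| Clinic | Linear predictor |
|---|---|
| Trial, not yet coached | μ + β_j |
| Trial, coached | μ + β_j + δ |
| TAU | μ + β_j + θ + λ_j |

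Coached minus not-yet-coached is δ. Coached minus TAU is δ − θ − λ_j. A test of δ = 0 is not a test of the second line against the third.

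**Step 3. What the TAU data contribute to δ.** The GLS weights of the δ estimate sum to +1 over coached trial half-years, −1 over uncoached trial half-years and 0 over TAU clinics.

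- TAU-by-time included: with period-specific terms every TAU weight is zero. SE(δ) is 0.0054, exactly as in step 1 with no TAU clinics; a linear interaction gives the same SE.
- No interaction, shared β_j: TAU period weights run from about +0.41 to −0.41 and sum to zero. TAU clinics enter through the trend only, and SE(δ) falls to 0.0035–0.0037.

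**Step 4. Illustration.** Let uncoached trial half-years run at 0.23, and coached and TAU clinics both at 0.2139. The coached-versus-TAU difference is 0, while δ = −0.0161. The test of δ rejects with probability of about 85% (interaction included) to 99% (no interaction). If instead uncoached trial half-years are at 0.25, coached at 0.2339 and TAU at 0.2139, coached clinics are worse than TAU by 0.02, and δ is still −0.0161 with the same SE. With no coaching effect, trial clinics at 0.2139 and TAU at 0.23, δ = 0 although the coached clinics' rate is lower.

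**Step 5. Precision of the actual contrast.** Clinic variation alone gives √(0.008855/35 + 0.008855/536) = 0.0164. The full calculation for δ − θ − λ_j in the last period gives about 0.017, and 0.0166 for δ − θ without the interaction. That is about 3 times SE(δ) with the interaction and about 4.5 times without it. The detectable difference is 2.80 × 0.0166 = 0.0465, or 0.23 to about 0.184: an RR of about 0.80 if TAU clinics are at 0.23. Between ICC 0.01 and 0.10 the SE of the contrast runs from 0.008 to 0.024. Choosing 515 or 536 TAU clinics, or 80 to 350 clients each, changes little.

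**The case against.** The best defence is that δ was never meant to compare levels. The closing sentence of the paragraph reads it properly, against what time alone would give, and the article says the added clinics supply a further estimate of the trend. Where period effects are shared, δ is indeed partly a difference in changes between coached and TAU clinics, which is a legitimate comparison with TAU. This stands for the model without the interaction. It does not rescue the sentence, because the same sentence adds the TAU-by-time interaction, which removes that borrowing, and because the Abstract and Materials and methods describe a comparison of outcomes with the non-participating clinics.

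It is also fair that the illustration uses assumed TAU rates, that in its first two cases coaching truly lowers events within trial clinics so that rejecting δ = 0 is correct for that question, and that the test is called post-hoc.

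A reader might go further and infer that the same evidence is counted twice in any event, or that the trial will announce superiority over TAU whatever the data. The documents do not support either. The test of δ repeats the randomised test only with the interaction in the model; with shared period effects the estimate and its SE differ from those of the 35-clinic model. How the result will be worded in publication is not stated.

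**Conclusion.** The point holds for the label and the choice of contrast. As specified, the named test cannot deliver the coached-versus-TAU comparison of outcomes, because the TAU level cancels from δ. With the stated interaction it is the randomised within-trial test again; without it, it is partly a comparison of changes. Under the assumed rates it rejects in about 85% to 99% of trials when coached and TAU outcomes are equal, and the contrast actually wanted has an SE roughly 3 to 4.5 times larger. The cancellation needs no numerical assumption. The sizes rest on the article's planning figures, a linear approximation, assumed TAU clinic sizes and illustrative TAU rates.

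This is a stated rule naming the wrong coefficient, not a detail left to an analysis plan. It should not be read as a fault in the primary analysis: δ remains valid for the randomised question, and the power figure reproduces.

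**What to change.** Replace the sentence on the post-hoc test with three statements.

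1. δ is the effect of coaching against not-yet-coached half-years within the trial clinics. It is reported once, as the randomised result, and is not a TAU comparison.
2. TAU versus coaching is the contrast δ − θ − λ_j at a named period, where λ_j is the TAU-by-time term. If change is what is meant, it is instead the coached clinics' change from the baseline half-year minus the TAU clinics' change over the same interval. Either way, the SE comes from the joint covariance matrix of the coefficients.
3. The TAU contrast is labelled non-randomised and non-confirmatory, because trial clinics enter by responding to invitations and announcements.

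The cost is a few sentences and one linear contrast from a model already planned; design, data and sample size do not change. The downside is that the comparison of outcomes with TAU clinics is much less precise than the result it replaces (SE about 0.017 at ICC 0.05), and the article should say so.

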## Materials and methods

### Project 3 aims: Conduct a stepped-wedge trial that includes two conditions: 1) 35 clinics receiving a performance coaching intervention and 2) a treatment as usual (TAU) condition for all clinics not participating in the intervention to examine the effect of the OTP intervention on THD, retention in care, and adverse events

The SPIRIT checklist was used as a guide for reporting this study protocol (Fig 1). To assess the impact of the OASAS QM2 strategy on care retention and adverse events using a stepped-wedge, mixed-methods design across SUD treatment clinics. Clinics will be recruited to participate in this stepped wedge trial by State partners via email invitations, announcements via State listservs, and announcements at relevant meetings to contact the Project Manager or the Principal Investigators. A total of 35 clinics will be recruited after October 2025. The aim of the intervention is to help clinical staff interpret their quality measures and implement subsequent quality improvement efforts through facilitators. The intervention will be six months long for each clinic and be informed by the i-PARIHS model [95].

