**Fig 2 pone.0330882.g002:**
[figure not shown]
Stepped-Wedge Trial Diagram.

The intervention will be delivered to clinic leadership and staff. Zoom meetings with program directors will confirm enrollment and outline the timeline and expectations. We will use maximum variation purposeful sampling by recruiting clients from participating clinics in urban and rural locations as well as areas with variation in population characteristics. Clinic recruitment will be stratified by region (downstate, central, and western New York). Eligible clinics are OASAS-licensed specialty SUD outpatient programs serving at least 50 OUD clients annually. Further, we will recruit clients who are on a variety of MOUD schedules and ensure that we have representation based on gender, race, and ethnicity.

We will examine clinic staff and leadership’s perceptions of the intervention using surveys and semi-structured interviews [97–99]. The Klein implementation survey [100,101] will be administered to clinic staff at 6-months post-intervention. Semi-structured interviews (n = 72) will be conducted with at least one clinical and one member of clinic executive leadership at each clinic at the end of the six-month intervention phase. An interview guide will be created to reflect the dimensions of the i-PARIHS model [102–105]. In order to inform replication and dissemination of this intervention model, the Coaches will complete logs after each interaction with a study site [97]. Master’s-level interviewers with qualitative experience, supervised by Drs. [name] and [name], will conduct all ~ 60-minute interviews. Field notes will be recorded post-interview.

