*Statistical Analyses of the Proposed Stepped-Wedge Trial:* Analyses will begin with examination variable distributions, appropriate transformations, and patterns for, followed by formal imputation methods if needed [110–112]. We will use Generalized Linear Mixed Models (GLMM) for the stepped-wedge design [106].

*Power Analysis for Primary Outcome Statistical power:* Power estimation for specific outcomes was conducted using PASS 2022 software and Monte Carlo simulation [113]. Sample size and baseline rates (μ) were estimated using administrative data. For 80% power, α = 0.05, ICC = 0.05, and a 5-crossover-point stepped-wedge-RCT with 7 clinics starting at each point, power calculations indicate 80% power to detect a small decrease (RR = 0.93) in adverse events with 35 clinics and 350 clients per clinic per 6-month period (n ≈ 73,500 total observations). This corresponds to a decrease from 0.23 to 0.21 events per 6 months. In racial/ethnic subgroups (10% of clients, n ≈ 35 per site), power remains 80% to detect a modest decrease (OR=0.78), from 0.23 to 0.18.

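### The TAU-expanded model lets about 515–536 non-randomised clinics help set the time trend behind the intervention effect, without fixing whether TAU-by-time terms are in that model or which estimate is primary

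*Protocol article*

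**What the plan says.** Quantitative Methods first sets out a GLMM for the stepped wedge, with period effects β_j, one intervention effect δ, and random effects for clinic and patient. It then adds the non-participating clinics:

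- **Level term.** "TAU clinics will be included in the model with an indicator variable".
- **Coding.** "For TAU clinics, the intervention indicator will be coded 0 in all periods". The article presents this as a further source of information on β_j from far more clinics, and then interprets δ as the change beyond what time alone would produce.
- **Interaction.** A TAU-by-time term is mentioned as a way to look at trends among TAU clinics. Nothing says whether it belongs to the model that yields δ.
- **Priority.** Neither the 35-clinic δ nor the expanded-model δ is named as primary. The Abstract, the Introduction and the Project 3 aims all present the non-participating clinics as the comparison condition.

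The two groups are formed differently. Under Project 3 aims: "Clinics will be recruited to participate in this stepped wedge trial by State partners via email invitations", along with listserv and meeting announcements. In Materials and methods, after Fig 2: "Eligible clinics are OASAS-licensed specialty SUD outpatient programs serving at least 50 OUD clients annually". TAU is every clinic not taking part, with no such floor stated.

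**The concern.** Within the 35 clinics, the timing of coaching is randomised, so δ is separated from time by design. Once TAU clinics share the same β_j, they also tell the model what the trial clinics would have done without coaching. The TAU indicator removes a constant difference between the groups but not a difference in trend. Clinics that respond to an invitation to quality coaching may be on a different path from the rest. Any such difference would load partly onto δ, while the smaller standard error would make the result look more secure. If trial clinics improved faster anyway, the effect would be overstated; if slower, a real benefit would be masked.

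The two statements about TAU also pull against each other. Extra information on β_j helps δ only if trends are shared; a TAU-by-time term in the same model removes that sharing.

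**Working it through.** **Inputs from the article**
- Power Analysis: "For 80% power, α = 0.05, ICC = 0.05"; "5-crossover-point stepped-wedge-RCT with 7 clinics starting at each point"; 350 clients per clinic per half-year; baseline 0.23; RR 0.93, so a planned effect of 0.23 × 0.07 = 0.0161 (1.6 points).
- TAU clinics: 571 − 35 = 536 (Materials and methods), or 550 − 35 = 515 (Component 2).
- The design text instead has clinics "randomized into six cohorts of six-month long interventions over three years", so six steps were run as well.

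**Assumptions**
- TAU cell size is not stated. 91,000 / 571 ≈ 159 clients per clinic per year, about 80 per half-year; range used 80 to 350.
- Two-sided α; proportion scale; GLS on clinic-period means; no separate patient effect.
- Cluster autocorrelation (CAC) 1, 0.9 and 0.8. The printed predictor has no clinic-by-period term, although a γ_ij distribution is listed beside it.

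**Step 1: the plan's own figures.** 35 × 350 × 6 = 73,500, as stated, with trial clinics only. For the Hussey-Hughes variance:
- p(1−p) = 0.1771; τ² = 0.05 × 0.1771 = 0.008855; σ² = 0.95 × 0.1771 / 350 = 0.000481.
- I = 35, T = 6, U = 105, W = 2,695, V = 385.
- Var(δ) = Iσ²(σ² + Tτ²) / [(IU − W)σ² + (U² + ITU − TW − IV)τ²] = 0.000902 / (980 × 0.000481 + 3,430 × 0.008855) = 2.92 × 10⁻⁵.
- SE = 0.00541. Detectable difference at 80% power = 2.80 × 0.00541 = 0.0151, so RR = 1 − 0.0151/0.23 = 0.934, matching the stated 0.93.

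**Step 2: add 536 TAU clinics with shared β_j and a TAU indicator (CAC 1).** SE falls to 0.00349 (350 per TAU cell) or 0.00368 (80 per cell). The weight w left on the randomised comparison is the variance ratio: (0.00349/0.00541)² ≈ 42%, or (0.00368/0.00541)² ≈ 46%. The other 54–58% is the contrast of trends between groups. Over all settings (5 × 7 or 6 × 6; 515 or 536 clinics; 80 or 350 per cell; CAC 0.8 to 1; with or without the indicator) it is 52–60%.

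**Step 3: bias from a trend difference.** Suppose trial clinics improve g points per period faster than TAU, with no coaching effect. The share of trial clinics coached rises by 1/5 per period, so the between-group contrast reads this trend as an effect of −5g. Hence bias = −(1 − w) × 5g. False-positive rate = Φ(|b|/SE − 1.96) + Φ(−|b|/SE − 1.96).

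| g (points per half-year) | Bias (points) | False positives, CAC 1 |
|---|---|---|
| 0.1 | −0.27 to −0.29 | 11–13% |
| 0.25 | −0.67 to −0.73 | 45–55% |
| 0.5 | −1.34 to −1.46 | 95–99% |

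For g = 0.25: (1 − 0.46) × 1.25 ≈ 0.67 and (1 − 0.42) × 1.25 ≈ 0.73, which is 42–45% of 1.6 points. Against the article's rounded drop from 0.23 to 0.21 (2 points), it is 34–36%. At CAC 0.9, correctly modelled, with 80 per TAU cell, SE is 0.00599 and bias −0.70 points; |b|/SE ≈ 1.17, so false positives are 22% (23% with 350 per cell).

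With six steps the multiplier is 6: w = 43–48% gives a bias of −0.78 to −0.85 points at g = 0.25.

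**Step 4: add the TAU-by-time interaction to the same model.** With a linear or a categorical term, SE is 0.00541, w = 100% and the bias is 0. That is the 35-clinic result. The linear term is enough here because the coached share itself rises linearly.

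**The case against.** The best defence is that the indicator and the TAU-by-time interaction appear in adjacent sentences and can be read as terms of one model. On that reading there is no bias from a linear trend difference. The 35-clinic GLMM is also written first, the TAU analysis is described as an expansion of it, and power rests on the 35 clinics alone. A journal article may leave the ranking of analyses to a fuller document. Planned adjustment for individual and community factors could shrink trend differences due to case mix. No document gives a trend difference, so 0.25 points is a chosen value.

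Much of this stands and limits the point. It does not remove it. The article does more than leave the matter open: it claims that TAU clinics add information on β_j and reads δ against it, which is true only without the interaction.

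A reader might infer three stronger things that the article does not support:
- **That δ loses the protection of randomisation.** Even with shared β_j, 40–48% of the weight stays on the randomised comparison.
- **That no randomised-only analysis is planned.** The 35-clinic model is there; it is just not named as primary.
- **That the trial clinics do have a different trend.** Recruitment by invitation makes it plausible, but nothing documents it.

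**Conclusion.** The point holds as a defect in how the expanded model is specified. Under shared β_j, a small majority of the information on δ (52–60%) is non-randomised, and a modest trend difference could produce a biased and falsely precise result. Under the interaction reading there is no bias, but the stated benefit for δ is empty. The text cannot deliver both, and leaving the choice open allows it to be made after results are seen.

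The share depends on the assumed TAU cell size and CAC but moves little over the ranges tried; using 515 or 536 TAU clinics, or five or six steps, does not change the conclusion. The bias and false-positive figures depend directly on the assumed trend difference and show sensitivity; they are not forecasts.

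**What to change.** 1. Name δ from the 35 randomised clinics as the primary estimate, matching the power calculation.
2. Keep the shared-β_j expanded model as a supportive analysis, labelled partly non-randomised. Ideally limit TAU to clinics meeting the same floor of 50 OUD clients a year.
3. Report the TAU-by-period interaction as the check on whether sharing β_j is justified. The δ from a model with full TAU-by-period terms is the randomised estimate, so it should not be labelled non-randomised.

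**Cost.** A few sentences of analysis text. The primary estimate gives up precision borrowed from TAU (SE about 0.0054 instead of 0.0035–0.0037, at CAC 1). The power statement counted only 35 × 350 × 6 = 73,500 observations, so no stated power is lost.

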If we observe significant treatment effects (e.g., reduced adverse events) from the performance coaching intervention, we will conduct follow-up analyses to strengthen causal inference. Drawing on methods from treatment mechanism research, we will test whether hypothesized mediators (e.g., person-centered care, retention in treatment) are associated with outcomes. We will also examine moderation by population characteristics and regional variation (e.g., gender, location), as well as provider-level differences in implementation. Lagged treatment effects will be assessed using interaction terms between treatment and time since intervention start by cohort. These exploratory analyses will inform interpretation and guide qualitative inquiry.

*Data and specification:*

We will join multiple administrative data sources from New York State for years 2021–2027 to form our analytical dataset. We will use Client Data System (CDS), Medicaid claims, and NYS vital statistics data to form the analytic dataset. The OASAS treatment registry (CDS) will provide extensive clinical data on clients at treatment admission and will include descriptions of providers through the provider data system (PDS). Medicaid will provide medical diagnoses, healthcare services, SUD treatment services, and medication utilization data. The New York State Vital Statistics will be received from the outpatient clinics in the form of all-cause mortality for clients participating in the trial. Additional OASAS data will provide operational and staffing information for each clinic. To date, 75% of clients in the OASAS registry have been linked to Medicaid claims data.

Quality measures from Project 1 will encompass patient, clinic, and organizational factors, including demographics, clinical complexity, substance use patterns, prior healthcare utilization, community access, substance use trends, resources, psychosocial interventions, clinic structure, staffing, and MOUD use and retention. Primary outcomes include adverse events, healthcare utilization, and mortality. Adverse events are defined as SUD-related hospitalizations or emergency department visits, including overdose, within 12 months of treatment entry. Healthcare utilization includes all-cause emergency department visits or hospitalizations within the same timeframe. Mortality will be assessed as all-cause mortality. Outcome variables will be risk-adjusted to account for client health status.

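### The only stated mediator test is association with outcome, which cannot tell a mechanism of coaching from a factor that is merely prognostic

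*Protocol article*

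**What the plan says.** The follow-up analyses are described under Data and analytic plans, Project 3: Stepped-wedge trial.

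- Condition for running them: "If we observe significant treatment effects (e.g., reduced adverse events) from the performance coaching intervention".
- Purpose: "we will conduct follow-up analyses to strengthen causal inference".
- The mediator test, introduced as drawing on treatment mechanism research: "we will test whether hypothesized mediators (e.g., person-centered care, retention in treatment) are associated with outcomes".
- Status: "These exploratory analyses will inform interpretation and guide qualitative inquiry".

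The coaching indicator is defined in the same section as "coded 0 for the control condition, then 1 from the start of the intervention in the clinic until the end of the study". The paragraph on mediators does not mention it, and it does not mention an indirect effect.

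Elsewhere, the Introduction and the Project 3 aims name retention in care among the things on which the intervention is to be evaluated. The mediator paragraph does not refer back to that. For person-centered care, the other mediator named, the article nowhere states an estimate of the effect of coaching.

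**The concern.** Whether coaching worked through a mediator depends on two links: coaching changes the mediator, and the mediator changes the outcome. The stated test addresses the second link only. Its null hypothesis is that mediator and outcome are unrelated, whereas the null hypothesis for a mechanism is that the indirect effect is zero.

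Suppose person-centered care truly lowers adverse events. The association would then be present in control periods as well as coached ones, and finding it would say nothing about coaching. Running the test only after coaching has shown an effect on adverse events does not help, because that effect may have come about by any other route.

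If coaching succeeds, readers will ask how. Followed as written, the analysis could direct the interpretation and the qualitative work towards a component that coaching never altered.

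**Working it through.** **1. The plan's own figures.** The power paragraph gives "For 80% power, α = 0.05, ICC = 0.05, and a 5-crossover-point stepped-wedge-RCT with 7 clinics starting at each point", then "35 clinics and 350 clients per clinic per 6-month period (n ≈ 73,500 total observations", and "This corresponds to a decrease from 0.23 to 0.21 events per 6 months".

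- Observations: 35 × 350 × 6 periods = 73,500, as stated. (The design description mentions seven periods. That does not affect what follows.)
- Target: 0.23 × 0.93 = 0.2139, a difference of 0.0161.
- Hussey-Hughes variance with I = 35 clinics, T = 6 periods, U = 105, W = 2,695, V = 385: Var = I·s²(s² + Tτ²) / [(IU − W)s² + (U² + ITU − TW − IV)τ²], where IU − W = 980 and the second bracket is 3,430.
- Total variance 0.23 × 0.77 = 0.1771, so with ICC 0.05 τ² = 0.008855 and s² = 0.95 × 0.1771 / 350 = 0.000481. The SE is 0.0054.
- Power = Φ(0.0161 / 0.0054077 − 1.96) = Φ(1.017) ≈ 84.5%, two-sided 0.05 assumed. Other standard variants with binomial variance give 80% to 85%, and the risk ratio detectable at 80% power is 0.932 to 0.935. The stated RR of 0.93 is reproduced. The article gives no figure for the mediator test.

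**2. How readily the association test is significant.** Wald approximation for a binary patient-level mediator with prevalence p (assumed 50% or 30%) and independent observations:

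SE(log OR) = 1 / √(73,500 × 0.23 × 0.77 × p(1 − p)), which is 0.0175 at p = 0.5 and 0.0191 at p = 0.3. Power = Φ(|ln OR| / SE − 1.96).

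| Mediator-outcome OR (assumed) | p = 50% | p = 30% |
|---|---|---|
| 0.98 | 21% | 18% |
| 0.95 | 83% | 77% |
| 0.93 | 98.5% | 97% |
| 0.90 | >99.9% | >99.9% |

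No coaching term enters this calculation. The OR giving 95% power is 0.94 (p = 50%) or 0.93 (p = 30%). If correlation between observations costs a design effect of 5, it is 0.87 or 0.86. With a design effect of 10, it is 0.82 or 0.80.

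**3. Simulation with coaching having no effect on the mediator.** There were 1,000 trials per row: 35 clinics, 6 periods, 350 clients per clinic-period, and a coaching OR of 0.90 on outcome by another route (assumed). The analysis used clinic and period fixed effects with clinic-robust standard errors. *Both links* means that the coaching-to-mediator effect is also significant.

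| Mediator level | OR | Association test | Both links |
|---|---|---|---|
| Patient | 1.00 | 5.0% | 0.4% |
| Patient | 0.95 | 76.7% | 4.8% |
| Patient | 0.90 | 100% | 5.0% |
| Patient | 0.80 | 100% | 5.3% |
| Patient | 0.70 | 100% | 6.0% |
| Clinic-period | 1.00 | 5.0% | 0.2% |
| Clinic-period | 0.95 per unit | 32.4% | 2.6% |
| Clinic-period | 0.90 per unit | 82.2% | 4.2% |
| Clinic-period | 0.80 per unit | 100% | 5.7% |
| Clinic-period | 0.70 per unit | 100% | 5.0% |

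A separate simulation of 500 trials, stratifying on clinic-period, gave 81% at OR 0.95 and 100% at 0.90 for a patient-level mediator.

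**4. Does the condition of a significant coaching effect protect?** Among simulated trials that met it, the patient-level association was significant in 76.9% at OR 0.95 and 100% at 0.90 or stronger. These match the unconditional rates, so the condition filters nothing.

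**The case against.** The strongest reply has five parts.

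*Retention is already covered.* The effect of the intervention on retention in care is a stated trial aim, so for that mediator all the relations are somewhere in the article. This stands. What is missing is the connection to the mediator test. For person-centered care the coaching link is not stated at all.

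*It is exploratory, with no decision rule.* This also stands. The article does not say that a significant association will be declared a mechanism. A reader might infer that the plan would name person-centered care as the way coaching works, but the document does not say so. The label limits the consequence to interpretation. It does not make the test answer a different question.

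*An article condenses.* Model terms for a conditional follow-up are commonly left to a fuller document, and the text does not exclude the coaching indicator. But the article does state the hypothesis to be tested and its purpose, and the two do not match. An analysis plan that followed the sentence faithfully would carry the mismatch forward.

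*The rates are power to detect a real association.* This is correct. A reader might infer that the test supports a coaching mechanism almost every time. That is not a property of the test: it depends on the assumed strength, level and prevalence of the mediator, none of which the document gives.

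*A product of logit coefficients is not in general the indirect effect.* This is correct, and the fix below avoids it.

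**Conclusion.** The point holds in a limited form. The stated test covers only the mediator-outcome link and cannot separate a mechanism of coaching from a prognostic factor, although its stated purpose is causal. This is clearest for person-centered care.

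The size is conditional. For a patient-level mediator with an odds ratio of about 0.93 or stronger, at about 73,500 independent observations and 30% to 50% prevalence, the test will usually be significant (97% or more) even if coaching left the mediator unchanged. The logical gap does not depend on these assumptions, but the percentages do.

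It would also go too far to say that coaching plays no part: it enters as the condition for running the analysis, and its effect on retention is a trial aim. The primary analysis is untouched. This is a cheap improvement to an exploratory analysis, worth making before results are seen.

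**What to change.** Restate the mediator analysis as follows.

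1. For each hypothesized mediator, estimate the effect of coaching on it with the stepped-wedge model (X_ij, period and clinic effects). For retention, use the estimate already implied by the trial aims.
2. Estimate the mediator-outcome relation with X_ij and period kept in the model.
3. Interpret the mediator as a possible mechanism only if both links are supported (joint significance), or if the interval for an indirect effect on the risk scale excludes zero. Obtain that effect by model-based standardisation with a clinic-level bootstrap, not as a product of logit coefficients.
4. Otherwise report the association as prognostic only. Keep the exploratory label throughout.

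The cost is one extra model per mediator on data already planned. Randomisation, data collection and the primary analysis do not change. The downside is that a mechanism claim becomes harder to make and less precise. The mediator is still not randomised, so confounding between mediator and outcome remains a caveat.
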